### Statistical analyses

2.9

Outcomes will be analyzed with a full analysis set (FAS) and per protocol set (PPS). The FAS targets all participants whose heights can be measured after starting the intervention and have no major violation of inclusion criteria. PPS targets all the participants who have been treated with the massage chair for >118 days (70% of the total 168 days). The safety analysis targets all participants with available safety data obtained by phone or visit.

Continuous data will be arranged as representative values such as mean and standard deviation. Height percentile, height SDS, predicted adult height, seated height-to-standing height ratio, and BMI will be tested by using the paired *t* test or Wilcoxon signed-rank test. The final height and weight will be measured by using a 1-sample *t* test or Wilcoxon signed rank-test from the parameters after 24 weeks of initial percentile. The final bone age will be tested by using a 1-sample *t* test or Wilcoxon signed rank-test, from the age after 0.5 years of the initial bone age. AEs will be described as frequency, percentage, and 95% confidence interval for the occurrence rate in all the participants. The difference in the incidence of AEs between before and after intervention will be tested by using a *χ*^2^ test or Fisher exact test. A secondary analysis will be conducted by grouping according to boys, girls before menarche, and girls after menarche. If necessary, analysis of covariance will be used.

The significance level is 0.05 for all the statistical tests, and 2-tailed tests will be performed. Missing values will be imputed using the last-observation-carried-forward method.

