We prepared a prospective study to investigate the effects of a massage chair on growth by comparing with national standard statistical data. The results will provide information on the potential effects of the massage chair on growth stimulation and the possible adverse events (AEs) associated with the use of the chair in children.

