### Study design

2.2

This is a prospective single-group study protocol that will include children aged 11 years with average height. It aims to observe the potential of a 24-week massage for growth promotion. The study protocol conforms to the Standard Protocol Items: Recommendations for Interventional Trials.

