#### Height

2.8.1

Height will be measured with the participant barefoot, and the value will be rounded off to 2 decimal places. Height will be measured by a trained nurse at the same time of day (±1 hour) to reduce height deviation during the day. Height will be measured with a portable stadiometer (Seca 213, Seca GmbH, Hamburg, Germany) that can measure heights ranging from 20 to 205 cm. Height will be measured from screening to close-out.

Height percentile and standard deviation score (SDS) will be based on the 2017 Korean growth chart.^[14]^ Values outside 3 standard deviations from the median of the height were removed to avoid biased calculation. The height percentile was smoothed by Loess regression (Proc Loess in SAS 9.4) for removing fluctuation associated with age or height. The values were converted to normal distributions by applying the Box-Cox transformation.

Growth rate will be calculated by dividing the height difference by the number of days required. The seated height-to-standing height ratio will be determined by measuring height in the seated position with Seca 213.

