#### Weight

2.8.3

Weight will be measured in light clothing and the value will be rounded off to 2 decimal places. Weight will be measured by a trained nurse using a load cell scale (Jenix DS-103 M) that can measure weights ranging from 10 to 200 kg. Weight will be measured from screening to close-out. Body mass index (BMI) will be calculated by dividing the weight by the square of the height.

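### Raw BMI and the raw seated-to-standing height ratio are tested against zero change in a single group of growing children, while height, weight and bone age are tested against expected growth

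*Protocol article*

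**What the plan says.** The Statistical analyses section sorts the growth outcomes into two kinds of test.

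- **Change from baseline.** "Height percentile, height SDS, predicted adult height, seated height-to-standing height ratio, and BMI will be tested by using the paired" t test or the Wilcoxon signed-rank test.
- **Comparison with expected progress.** Final height and weight go to a one-sample test whose reference value is taken "from the parameters after 24 weeks of initial percentile". Final bone age is likewise compared with a reference value, taken "from the age after 0.5 years of the initial bone age".

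The outcome definitions show which measures are already adjusted for age. Under Height: "Height percentile and standard deviation score (SDS) will be based on the 2017 Korean growth chart". The other two are raw. Under Weight: "Body mass index (BMI) will be calculated by dividing the weight by the square of the height". Under Height: "The seated height-to-standing height ratio will be determined by measuring height in the seated position with Seca 213". No percentile, SDS or expected value is given for either.

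On design: "This is a prospective single-group study protocol that will include children aged 11 years with average height". On the aim, the Introduction says: "We prepared a prospective study to investigate the effects of a massage chair on growth by comparing with national standard statistical data".

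**The concern.** In a single-group study of growing children, a paired test against zero attributes nothing to age. That does little harm for height percentile and height SDS, where age is already in the scale, or for predicted adult height, which is computed from height and skeletal maturity. It matters for raw BMI and the raw ratio. For these two, zero change is the right null only if a child of this age would show none over 24 weeks without the chair, and the article gives no ground for assuming that.

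The authors accept the principle elsewhere in the same paragraph, where expected growth is built into the null for height, weight and bone age. Among the tested growth outcomes, only BMI and the ratio have neither standardisation nor a reference value. For these two the promised comparison with national data does not take place.

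At stake is what the two p values can mean. A small one may reflect age alone. A large one may hide a chair effect that runs against the age trend.

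**Working it through.** **1. The article's own figure.** The only sample-size arithmetic is 30 children inflated for 20% dropout: 30 / (1 − 0.20) = 37.5, rounded up to 38. This reproduces the stated 38. The article gives no effect size, SD or power, so I use n = 30 and n = 38 below.

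**2. How much growth to expect.** The Discussion gives average heights for 11-year-olds of 144.7 to 150.8 cm (boys) and 145.8 to 151.3 cm (girls). I read each range as one year of growth. Follow-up is 168 days.

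- Boys: (150.8 − 144.7) × 168 / 365.25 = 2.8 cm
- Girls: (151.3 − 145.8) × 168 / 365.25 = 2.5 cm

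**3. What zero change in BMI requires.** From 150 cm, BMI stays constant only if weight rises by ((150 + gain) / 150)² − 1:

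- Boys: (152.8 / 150)² − 1 = 3.8%
- Girls: (152.5 / 150)² − 1 = 3.4%

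Nothing in the article says that weight rises by exactly this share.

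**4. What zero change in the ratio requires.** The trunk must take exactly its current share of the height gain. Assume a ratio of 0.52 and a trunk share s of the gain (neither is in the article). The change is (0.52 × 150 + s × gain) / (150 + gain) − 0.52. For s from 40% to 60% this is −0.22 to +0.15 percentage points in boys and −0.20 to +0.13 in girls. The range includes zero, so drift in the ratio is possible but not shown.

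**5. Rejection rate with no chair effect.** If the outcome drifts with age, the paired t statistic follows a noncentral t distribution with n − 1 degrees of freedom and noncentrality (drift / SD of change) × √n. Example: drift 0.3 SD, n = 30, noncentrality 0.3 × √30 = 1.64. At two-sided 0.05:

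| Assumed drift (SD of change) | n = 30 | n = 38 |
|---|---|---|
| 0 | 5% | 5% |
| 0.1 | 8% | 9% |
| 0.2 | 19% | 23% |
| 0.3 | 36% | 44% |
| 0.5 | 75% | 85% |

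In BMI units, an assumed drift of 0.3 kg/m² with an SD of change of 0.7 gives 62% at n = 30 and 73% at n = 38. Over drifts of 0.1 to 0.4 and SDs of 0.5 to 0.9, the n = 30 figure runs from 9% to 99%. For the ratio, drifts of 0 to 0.3 points and SDs of 0.4 to 0.8 give 5% to 98%. These ranges show that the error rate depends almost wholly on unknown inputs. They do not estimate it.

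**6. Masking.** The test sees only drift plus chair effect. If the two are equal and opposite, the sum is zero and the test rejects 5% of the time, however large the chair effect.

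**The case against.** - **The limitations already cover it.** The Discussion concedes that without a local comparison group a growth effect cannot be established, and calls the study a pilot. This stands against the inference that the authors would present a p value here as proof of a device effect; the article does not say so. It does not repair the test, because the same limitation says the data will be compared with national figures, and for these two outcomes the planned test makes no such comparison.
- **Weight and height are handled properly.** Both components of BMI are tested against expected values, and weight percentile is also listed in the Discussion. A BMI change with both components on track could be recognised as ordinary growth. This stands, and it lowers the severity.
- **Drift in the ratio is not shown.** This stands. A reader might infer that both measures are known to shift at age 11. The article gives no such figure for the ratio, and the range in step 4 includes zero. The planned split by sex and menarche would show differing directions, but it supplies no reference.
- **The ratio might be thought the outcome closest to the mechanism.** The Intervention section does not support that. It combines lower-body and whole-body modes, gives height growth as the purpose and predicts no direction for the ratio. The height outcomes lie closer to that purpose, and they are age-referenced.
- **Covariance analysis is held in reserve, and an analysis plan may say more.** The covariance option is unspecified and brings in no external reference. The test for these outcomes is a stated choice, so this is not a matter of missing detail.

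**Conclusion.** The point holds as a moderate inconsistency. It is firm for BMI and conditional for the ratio. The null of zero change does not fit raw, age-dependent measures in an uncontrolled study of growing children, and it departs from the approach used for height, weight and bone age in the same paragraph.

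The size cannot be fixed from the article. It gives no normal 24-week change and no SD of change for either outcome, so every rejection rate above except the 5% at zero drift rests on assumption. A modest assumed drift of 0.2 SD would raise the rate from 5% to about 19% at n = 30.

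A reader might infer that a significant result carries no information, or that the plan must be changed before it can go ahead. Neither is supported. A significant result would still show that the measure changed, but could not say whether age or the chair was responsible. The problem also touches two derived outcomes in a self-described pilot and leaves the design, the sample size and the main height analysis unaffected.

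**What to change.** - **BMI.** Replace the paired test on raw values by a test of change in age- and sex-specific BMI SDS or percentile. Alternatively, test final BMI against its expected 24-week value on the child's initial percentile, as is already planned for weight. Either way normal drift moves into the null, and the error rate returns to 5% to the extent that the reference describes these children. This assumes that the national reference covers BMI; the article cites the 2017 Korean chart only for height. If it does not cover BMI, report the change descriptively with a 95% CI.
- **Seated-to-standing ratio.** Report the change with a 95% CI for boys, girls before menarche and girls after menarche, the groups already planned, with no test against zero. If an age- and sex-specific reference is available, form an SDS and test that.
- **Wording.** State that a change in either raw measure is not by itself evidence for or against the chair.

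The cost is analysis wording and, for BMI, a reference table. No new measurements are needed. The ratio loses its p value, and BMI may lose its own if no reference is found.

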### Participants

2.3

Thirty-eight children from Kyung Hee University Medical Center will be recruited through posters and banners. The participants and their guardians will receive research information such as objectives, procedures, and potential benefits and harms through standardized dialogues. Informed consent will be acquired from the children and their guardians ahead of the screening process. The participants will be allowed to withdraw from the study at any time they want. The research procedure will be conducted as shown in Figs. 1 and 2. All the participants will undergo a massage chair treatment at home for 24 weeks. After the screening session, 4 assessment visits will be planned for the children. The guardians will receive text messages as reminders of the scheduled visits.

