#### Bone age

2.8.2

On hand radiography at visits 2 and 5, bone age will be computed using the Tanner-Whitehouse (TW) method. The maturity of the hand ossification centers will be assessed as a radius-ulnar-short bone (RUS) score from 0 to 1000 as compared with the bone age chart according to sex and age.^[15]^ Two-year-old boys have a RUS score of 42, and 2-year-old girls have a RUS score of 126. The RUS score of 1000 is computed for 16.5-year-old boys and 15.0-year-old girls. The TW3 RUS score was based on the American, Argentine, Belgian, British, Italian, Japanese, and Spanish surveys between 1960 and 1995. The TW3 RUS score will be calculated by researchers who have been trained for > 3 months before assessment.

Predicted adult height will be calculated from the measured height and RUS score using the TW3 equations, which were developed according to boys, girls before menarche, and girls after menarche. The height SDS for bone age will be determined according to the 2017 Korean growth chart.

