## Discussion

3

Massage had some effects on growth in randomized controlled trials (RCTs) or quasi-RCTs.^[16]^ It was used alone or with swimming, oral administration, plaster therapy, or auricular acupuncture. The most frequently used massage method was spine pinching, which promotes gastric fluid secretion, gastrointestinal peristalsis, and digestive ability for carbohydrates and proteins. However, previously studied growth-promoting massages have individual differences in effect depending on the skill of the practitioner, due to the nature of manual therapy. This is the first study to verify the effect of standardized massage using massage chair on growth by stimulating the spine and knees with fixed strength and frequency.

BEG-100 targets children whose heights range from 130 to 170 cm, but it is most appropriately manufactured for a 150-cm height. We determined to enroll 11-year-old Korean children because the average heights of 11-year-old Korean boys range from 144.7 to 150.8 cm and those of 11-year-old Korean girls range from 145.8 to 151.3 cm. The intervention period was set to be 24 weeks, which is the most frequent intervention period in previous studies that reported the effect of massage on growth. Standing and seated heights will be measured to see changes in height, height percentile, height SDS, growth rate, and seated height-to-standing height ratio. Hand radiography will be performed to identify changes in bone age, predicted adult height, and height SDS for bone age. Through weight measurements, we will confirm changes in weight, weight percentile, and BMI. The safety of BEG-100 will be investigated through a comparison of voluntarily reported AEs before and after the intervention.

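### Final bone age is tested against a fixed 0.5-year advance, although the intervention lasts 24 weeks (0.46 year)

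*Protocol article*

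**What the plan says.** All places are in the protocol article.

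- **Length of treatment.** The Discussion states: "The intervention period was set to be 24 weeks". Section 2.9 defines the per-protocol threshold as "70% of the total 168 days", which is the same 24 weeks in days.
- **Timing of the films.** Section 2.8.2: "On hand radiography at visits 2 and 5, bone age will be computed using the Tanner-Whitehouse (TW) method". Section 2.3: "After the screening session, 4 assessment visits will be planned for the children". If screening is visit 1, visits 2 and 5 are the first and last assessments.
- **Bone-age test.** Section 2.9: "The final bone age will be tested by using a 1-sample *t* test or Wilcoxon signed rank-test", and the reference value is taken "from the age after 0.5 years of the initial bone age".
- **Height and weight tests.** The sentence just before that takes their reference values "from the parameters after 24 weeks of initial percentile".
- **Use of actual time.** Section 2.8.1 does use it, for one derived outcome: "Growth rate will be calculated by dividing the height difference by the number of days required".

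**The concern.** Adjacent sentences give what appears to be one follow-up period two lengths: 24 weeks for height and weight, and half a year for bone age. Half a year is about two weeks longer than the treatment period.

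This matters more here than it would in a controlled trial. The study has a single group, so no control arm cancels a timing error. For bone age, the 0.5-year advance is the null hypothesis itself. If it is set too high, a group maturing exactly in step with the calendar falls below it on average, and the test is more likely to report that bone age advanced less than expected.

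**Working it through.** **Inputs from the article.** Treatment period 24 weeks = 168 days (2.9, Discussion). Null advance 0.5 year (2.9). Two-sided alpha 0.05 (2.9). Sample size 30 as the base figure and 38 after allowance for 20% dropout (2.4): 30/0.8 = 37.5, rounded up to 38, so the stated total reproduces.

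**Assumed inputs.** The interval from visit 2 to visit 5 is 168 days. With no device effect, bone age advances one year per calendar year. The SD of bone-age change is not given, so a range of 0.2 to 0.6 year is shown.

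**Step 1: can 0.5 year be reproduced?**

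- 168/365.25 = 0.460 year.
- 0.5 × 365.25 = 182.6 days, and 182.6/7 = 26.1 weeks.

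The figure of 0.5 is reached only by rounding 0.46 to one decimal or by treating 24 weeks as six months.

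**Step 2: size of the discrepancy.**

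- 0.5 − 0.460 = 0.040 year.
- 182.6 − 168 = 14.6 days.
- 14.6/168 = 8.7% of the interval.

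**Step 3: effect on the one-sample t test.** When the true mean advance is 0.460 and the null is 0.5, the test statistic follows a noncentral t distribution with n − 1 degrees of freedom. The noncentrality, in absolute value, is 0.040/(SD/√n). For n = 30 and SD 0.3, SD/√n = 0.0548 and 0.040/0.0548 = 0.73. The false-rejection rate is the probability beyond the two-sided 5% critical values.

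| Assumed SD (years) | Shift/SE, n = 30 | Rejection rate, n = 30 | Rejection rate, n = 38 |
|---|---|---|---|
| 0.2 | 1.10 | 18.6% | 22.5% |
| 0.3 | 0.73 | 10.9% | 12.6% |
| 0.4 | 0.55 | 8.3% | 9.2% |
| 0.5 | 0.44 | 7.1% | 7.7% |
| 0.6 | 0.37 | 6.4% | 6.9% |

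Most of the rejections fall on one side. At n = 30 and SD 0.3, 10.5% are in the direction of slower bone age and 0.4% in the other.

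**Step 4: dependence on the actual interval.** The correct null moves with the dates: 161 days gives 0.441 year, 168 days gives 0.460 and 182 days gives 0.498. A fixed 0.5 is therefore nearly right only if the films are about 26 weeks apart.

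**Step 5: height and weight.** Their reference point is also a nominal time. At an assumed growth velocity of 5 to 8 cm/year, a final visit 7 days late adds 0.10 to 0.15 cm to the observed gain (velocity × 7/365.25), and an early visit removes the same amount. The article does not say whether visits tend to fall late or early.

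**The case against.** The strongest reply is that the interval between films is inferred. The 168 days describe treatment. The films are tied to visit numbers, and the timing of those visits is in Figure 2, which is not shown. The chair is delivered to the home after enrolment (2.7), so a visit-2 film could precede first use. With films about 26 weeks apart, 0.5 would be close to correct. This stands as a limit on the size of the error. It does not rescue the text: if height and weight are taken at the same visits as the films, a 26-week interval would put their 24-week reference value out instead.

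Second, 0.46 rounds to 0.5 and the gap is about two weeks. That is true, but a rounded null still shifts the test.

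Third, the rejection rates rest on an SD that the article does not give, and they are close to nominal at SD 0.5 to 0.6. They also assume calendar-pace maturation, although the bone-age reference comes from surveys in which Korea is not listed (2.8.2). Both points stand. However, the plan's own benchmark also appears to equate elapsed time with bone-age advance, so correcting the elapsed time adds no new assumption.

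A reader might infer three stronger conclusions that the document does not support:

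- **That the error favours the device.** The tests are two-tailed, and nowhere does the article say that slower bone age will be read as benefit. Predicted adult height is computed from measured height and the RUS score, so the 0.5-year null does not touch it.
- **That individual children would be scored as delayed.** Section 2.9 describes a group-level test and no such classification.
- **That height and weight are biased upwards.** That needs systematically late visits, which nothing indicates. The 24 weeks may simply name the final time point, and visit windows and the exact age for reference look-up are details that an article may leave to the full protocol.

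**Conclusion.** The 0.5-year null for bone age does not agree with the article's own 24 weeks, and this inconsistency depends on no assumed SD. If visits 2 and 5 bracket the intervention, the null is about 0.04 year (8.7%) too high and tilts the test towards slower-than-expected maturation. With n = 30 and calendar-pace maturation, the false-rejection rate would be somewhere between about 19% (SD 0.2) and 6% (SD 0.6) instead of 5%. Where it lies in that range cannot be settled from the document.

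No systematic bias is shown for height or weight. Bone age is one of many outcomes in a study that describes itself as a pilot and accepts that it cannot prove a growth effect without a comparison group. The point is therefore moderate to minor in severity, but the wording is wrong as it stands and should be corrected.

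**What to change.** Replace the constant in section 2.9. For each child:

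- expected bone age = initial bone age + (date of visit-5 film − date of visit-2 film)/365.25;
- difference = final bone age − expected bone age, tested against zero with the one-sample t test or signed-rank test already planned.

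This is right whatever Figure 2 shows. The same sentence should say how a child without a second film is handled. Under the planned last-observation-carried-forward rule, the visit-2 reading would count as zero advance.

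As a secondary alignment, take expected height and weight on the initial percentile at the child's exact age on the measurement date, in keeping with the actual-days rule used for growth rate.

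The cost is a sentence or two of analysis text. It needs no new measurement, only the dates of films and visits.

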#### AEs

2.8.4

To assess overall clinical safety, the researchers will collect all voluntarily reported AEs during each visit and record the name, date, severity, course, seriousness, causality, and treatment performed for the AE in the case report form. The participants and their guardians will be asked, “Has there been any AE since the last visit?” When the child does not report any AE, the severity is considered minor or nonexistent. If the reported AEs are not sufficient for the participant to drop out from the study, the severity is considered moderate. When the child has to withdraw from the study to undergo treatment for the AE, the severity is considered severe.

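### The before-versus-after adverse event test makes no allowance for observation time, so background illness can look like harm from the chair

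*Protocol article*

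**What the plan says.** Section 2.2 (Study design) describes one group: "This is a prospective single-group study protocol". Section 2.3 (Participants) fixes the treated period: "All the participants will undergo a massage chair treatment at home for 24 weeks". It describes one screening session followed by four assessment visits, without giving intervals.

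Under section 2.8.4 (AEs), "the researchers will collect all voluntarily reported AEs during each visit". Children and guardians are asked about events since the previous visit, and each event's date, seriousness and causality are recorded, among other items.

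Section 2.9 (Statistical analyses) plans frequency, percentage and a 95% confidence interval for AE occurrence. It then adds a test: "The difference in the incidence of AEs between before and after intervention will be tested" with a chi-square "test or Fisher exact test". The level is set for every test: "The significance level is 0.05 for all the statistical tests, and 2-tailed tests will be performed". In the same paragraph several continuous outcomes "will be tested by using the paired" t test or its signed-rank counterpart.

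The Discussion (section 3) gives the AE contrast its role: "The safety of BEG-100 will be investigated through a comparison of voluntarily reported AEs before and after the intervention".

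**The concern.** Two features of the stated test do not fit the design.

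- **Observation time.** Each visit collects whatever has happened since the last one, so the chance that a child has reported at least one AE rises with the length of the period. A comparison of incidence across two periods is fair only if they are equally long or the counts are divided by time. The section states neither condition. This is the damaging feature.
- **Pairing.** Chi-square and Fisher tests assume two independent groups, but here the same children fill both columns. The plan respects pairing for its continuous outcomes and not for AEs.

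At stake is the trial's stated safety comparison. A small p-value could arise from ordinary childhood illness over a longer period and be read as harm from the device. The study is described as a pilot for later randomised trials, so that misreading could carry into their planning.

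**Working it through.** **The plan's own figure.** Section 2.4 starts from 30 children and allows 20% dropout: 30 / (1 − 0.20) = 37.5, rounded up to 38. This reproduces, and 38 per column is used below. The article gives no figure for the AE comparison itself.

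**Inputs.**
- After period: w₁ = 24 weeks (section 2.3).
- Before period: not in the readable text; the schedule is in a figure not available here. Radiographs at visits 2 and 5 (section 2.8.2) suggest that visit 2 is baseline, so the before period is inferred to be screening to visit 2. Assumed w₀ = 1, 2 or 4 weeks.
- Background AE rate r: not in the document. Assumed 0.25%, 0.5%, 1% and 2% per child-week, the same before and after, so the chair does nothing.
- Two-sided level 0.05 (section 2.9).

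**Risk per period.** P(at least one AE) = 1 − exp(−r × weeks). For r = 0.01 and w₀ = 2, the before risk is 1 − exp(−0.02) = 2.0% and the after risk is 1 − exp(−0.24) = 21.3%. The proportions differ about tenfold with no device effect.

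**How few events are needed.** With no child affected before and k of 38 after, the two-sided Fisher p-value is 2 × C(38,k) / C(76,k).
- k = 5: 2 × 501,942 / 18,474,840 = 0.054.
- k = 6: 2 × 2,760,681 / 218,618,940 = 0.025.

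Six children reporting anything at all in 24 weeks would be enough.

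**Probability of a false signal.** Each pair (a, b) of affected children before and after is weighted by Binomial(38, p₀) × Binomial(38, p₁), and the weights are summed over all tables with p ≤ 0.05.

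| Rate per child-week | After risk | Fisher, w₀ = 1 | w₀ = 2 | w₀ = 4 |
|---|---|---|---|---|
| 0.25% | 5.8% | 2.0% | 1.8% | 1.5% |
| 0.5% | 11.3% | 22.1% | 19.1% | 14.4% |
| 1% | 21.3% | 75.5% | 66.9% | 51.7% |
| 2% | 38.1% | 99.0% | 96.7% | 87.1% |

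The uncorrected chi-square test, the other option named, rejects more often over w₀ = 1 to 4: 13% to 16%, 40% to 57%, 69% to 92%, and 92% to over 99% at the four rates. With 30 children per column, Fisher gives 7% to 10% at 0.5% and 35% to 55% at 1%.

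**Which defect causes it.**
- *Equal time.* With w₀ = 24, Fisher rejects in 2.8% of trials at both 1% and 2% per child-week, and chi-square in 4.8% to 5.7% over the four rates. The false signal disappears.
- *Pairing.* With equal periods and between-child variation in risk (gamma frailty with shape 0.5 or 1, mean 1 AE per child-year), chi-square rejects in 1.5% to 2.5%. Ignoring the pairing alone makes the test conservative.
- *McNemar on the unequal periods.* The exact test gives 15% to 22% at 0.5%, 51% to 76% at 1% and 85% to 99% at 2%, much as Fisher does.
- *Rates per child-week.* Under no effect, the after-period share of all events is 24 / (24 + w₀): 0.960, 0.923 or 0.857. An exact conditional binomial test of that share rejects in 1.0% to 3.1% over the table's grid, within the nominal 5%.

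**The case against.** The strongest reply is that both quantities behind the size are assumed. The background rate appears nowhere, and voluntary reporting may keep it low; at 0.25% per child-week Fisher stays below its nominal level. The visit schedule is in a figure that is not readable here, so the short before period is inferred. A look-back history at screening is conceivable, although no section describes one. This stands as a limit on certainty. It does not reverse the direction: even an 8-week before period gives Fisher 29% at 1% and 56% at 2% per child-week, and only a window near 24 weeks removes the imbalance.

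A reader might infer that background illness is bound to appear as harm, that the unpaired test produces the false signal, or that the p-value reflects nothing but follow-up length. The document supports none of these. The first depends on the unstated rate and window. The second fails the equal-time check. On the third, the p-value mixes follow-up length with any real device effect, which would also move it.

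It is also fair to say that the plan already reports AE frequency, percentage and a confidence interval, records causality, and has AEs monitored monthly (section 2.10). The Discussion admits the lack of a comparison group and calls the study a pilot. The error leans toward false alarm, not false reassurance, and the growth analyses are untouched. That lowers the priority, but it does not justify the test. Nor can the matter be left to a later analysis plan, since the article itself names the contrast and the test.

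**Conclusion.** The point holds. Section 2.9 compares AE incidence before and after in the same children with no allowance for observation time, and that can turn background illness into an apparent harm signal. For 38 children and no device effect, the Fisher false-signal probability runs from about 2% to 99% across assumed rates of 0.25% to 2% per child-week and assumed windows of 1 to 4 weeks. It exceeds one half throughout that window range once the rate reaches 1% per child-week. These figures assume a constant rate and rest on an inferred before period. The pairing error is real but secondary. This should be corrected before analysis; it does not undermine the trial as a whole.

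**What to change.** - Section 2.9: delete the before/after chi-square or Fisher test of AE incidence. Keep the planned frequency, percentage and 95% confidence interval, and add AEs per child-week on the chair, broken down by recorded causality.
- Discussion: reword the sentence on how safety will be investigated so that it matches.
- If a before/after contrast is kept: state the pre-intervention window and compare within-child rates per child-week, by conditional Poisson regression with a log-time offset. Replacing Fisher with McNemar is not sufficient.

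The cost is wording and a little analysis work. AE dates are already recorded; the start and stop dates of chair use must also be kept. The downside of a retained contrast is low precision for the before-period rate: with a 2-week window, 38 × 2 = 76 child-weeks against 38 × 24 = 912, so at 1% per child-week fewer than one event (0.76) is expected before the start.
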